## **Monitoring**

A data monitoring committee will not be needed because this is a low-risk intervention. The current project is not a medical trial and music and training holds little to no risk for the participants.

## **Handling and Reporting of Adverse Events**

Little is known on adverse effects of music and training interventions. Any adverse events will be reported. The current study asks for sensitive information such as the GDS questionnaire. Appropriate action will be taken if anyone has a score that indicates suicidality or severe depression. The GDS will only use coded ID, and be done on paper, as to minimize the risk of unwanted people getting insight. All adverse events will be noted and reported, including whether the event was serious; whether it was assumed related or unrelated to the intervention; and whether it was resolved.

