Research has shown that it is possible to prevent falls by exercising. An alternative intervention, which is helpful for the users, is exercise. There has been research on dementia and effects of exercise (Hulme et al., 2010) where training were considered an effective non-medical treatment compared to other non-medical treatments. In Bergen Municipality's report "Safe on Two Legs" Bergen Kommune (2010) reported that balance training and strength have the best results for preventing falls. In the report, more studies (Campbell, Robertson, Gardner, Norton, & Buchner, 1999; Helbostad, Leirfall, Moe-Nilssen, & Sletvold, 2007; Skelton, Dinan, Campbell, & Rutherford, 2005) displayed how inactive seniors who had not previously experienced falls had a good effect of one year's training. The training group reduced the number of falls by 30% compared with the control group. The effect of exercise was also greatest in the elderly with initial or established functional failure. People with Alzheimer's have functional failure of cognitive functions, languages, and the like. According to the Safe on Two Legs report (2010), muscle strength is the low-impact effect a muscle or muscle-group can develop. Muscle strength is something that decays when people get older, and the average muscle density of a person in their 60s is about 40% less than in a 20-year-old. In an article (Liu & Latham, 2009), it appears that elders that exercise strength become stronger and achieve better function in daily activities. Another study (Kalapotharakos, Michalopoulos, Tokmakidis, Godolias, & Gourgoulis, 2005) showed that two groups of elderly people who did use to exercise did better on functional tests after a training intervention. According to the Bergen Commune report, exercise for the elderly as for young people must be done 2-3 times a week with a certain intensity (8-12 repetitions and 3 sets) and be done for a minimum duration of 12 weeks to have an effect (2010).

The reason we want to do our study is the lack of good evidence-based qualitative research in the field of music therapy and neuroscience. Most of the research on AD patients is done in later stages of the disease, and it has been recommended to try and look at music intervention as a prevention of deterioration in AD. Therefore the current project will investigate the effect of music intervention on AD patients in early stages of the disease.

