## **Music Intervention**

The music intervention consists of singing lessons and choir practice. Singing lessons will take place once a week for each participant every week for about 12 months. The therapist will come home to the participant, or meet them at the day centre and similar places. Participants will be given CD or MP3 files (as they prefer) with audio files with warm-up exercises, play songs and the song they will learn with their voice. Self-produced music material from the institute will be given to the participants in a media format they prefer. Example material can be found here: <https://soundcloud.com/[name]/jeg-gikk-en-tur-pa-stien> All participants in the music intervention group will meet one to two times a month to sing the songs they have learned in the individual singing lessons together in a choir. The choir will take place in at a place devised by Bergen Municipality. The intervention is standardised (see Appendix A for a detailed schedule), but therapists are free to make small changes to adapt the individual.

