## **Control Intervention**

The control group will continue on medications and activities that they usually have. They will not be asked to quit training or music if they are currently participating in such activities.

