## **Assessment of Attendance and Fidelity**

Participation in the program will be documented by the therapists in charge of the intervention by simply marking if the participants attend the intervention. 80 % participation is required for inclusion in analysis.

Mid intervention we will also interview participants about how they like their therapist and the therapy, and if they are doing the interventions on their own at home. However, there will be no strict measures of whether they do the intervention on their own. This is encouraged, but not a must.

There will be a midway evaluation of therapists for both the active interventions. Here we will inquire if they overlapped in any way. Both will be asked the same questions:

«Did you use music?», «Did you use exercise?»

Then we will ask the participants the same questions about the therapy sessions. This includes double self-reports from therapists and participants. In addition we will ask participants for their compliance, or how much they practiced on their own.

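### No common method of finding adverse events is set for the three arms, and unequal study contact will probably under-count events in controls

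*Protocol*

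**What the plan says.** Protocol, Handling and Reporting of Adverse Events: "All adverse events will be noted and reported, including whether the event was serious", together with "whether it was assumed related or unrelated to the intervention; and whether it was resolved". The section names no collector, question, time point or interval for any arm. It also observes that "Little is known on adverse effects of music and training interventions".

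Protocol, Monitoring: a data monitoring committee is judged unnecessary, on the ground that "music and training holds little to no risk for the participants".

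The contact schedule is spread over several sections:

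- Music Intervention: "Singing lessons will take place once a week for each participant every week for about 12 months". Choir meetings follow once or twice a month.
- Exercise Intervention: a weekly group session, tours offered twice a month, and individual follow-up by a therapist before and after the programme.
- Control Intervention: "The control group will continue on medications and activities that they usually have". No study contact is described during the year.
- Assessment of Attendance and Fidelity: "There will be a midway evaluation of therapists for both the active interventions". Participants are also asked about their therapy at this point, and Other Measures places it at six months. Session staff are told to record attendance; no event log is mentioned.
- Secondary Outcomes: the tests are done before randomisation and after 12 months in all arms. At 12 months participants are also asked whether they still live at home.

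**The concern.** When no method of enquiry is fixed, events reach the record through whatever contact staff happen to have. Here contact is frequent in two arms and, as described, absent for a year in the third. The participants have a disease in which, by the protocol's own Background, episodic memory worsens, so unprompted recall of a year's events is a weak substitute for asking.

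A control who skips the 12-month tests has no later contact within the trial year. Under Ethical Challenges, an active participant may decline testing and still attend sessions. Relatedness is judged against the intervention, which controls do not have, so it cannot restore comparability.

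At stake is the credibility of adverse event counts by arm, and of any low-risk statement based on them. The protocol plans to release the intervention materials and to bring positive findings into municipal care. An analysis plan cannot repair the gap, because it cannot recover events that nobody asked about.

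**Working it through.** **No figure to reproduce.** The protocol states no adverse event rate and no detection rate for this trial.

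**Step 1: scheduled contacts after randomisation.** Inputs come from the Music, Exercise and Control Intervention sections, the six-month evaluation and the 12-month visit. I take 52 weeks for the year and assume full attendance.

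| Arm | Sum | Contacts |
|---|---|---|
| Music | 52 lessons + 12 to 24 choirs + 1 midway + 1 at month 12 | 66 to 78 |
| Exercise | 52 sessions + up to 24 tours + 1 midway + 1 at month 12 | up to 78 |
| Control | 1 at month 12 | 1 |

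Tours are only offered, so 24 is a maximum; without them exercise has 52 + 1 + 1 = 54. The therapist follow-up after the exercise programme is not counted. The imbalance does not depend on these details.

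**Step 2: effect on a reported ratio.** Let r be the true risk ratio (active/control), and let c be the probability that a control's event is detected divided by the same probability in an active arm. Then

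reported ratio = r / c.

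The protocol gives no value for c, so the values below are assumptions. r = 1 means no true difference. r = 0.7 borrows the 30% reduction in falls cited in the Background, as an example of a protective effect.

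| c | r = 1 | r = 0.7 |
|---|---|---|
| 1.0 | 1.00 | 0.70 |
| 0.9 | 1/0.9 = 1.11 | 0.7/0.9 = 0.78 |
| 0.7 | 1/0.7 = 1.43 | 0.7/0.7 = 1.00 |
| 0.5 | 1/0.5 = 2.00 | 0.7/0.5 = 1.40 |

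Whenever c is below 1 the ratio moves upward, against the active arm. The active arm looks worse than control only when c is smaller than r.

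**Step 3: the same in counts.** Take the recruitment target of 45 per arm, an assumed true control risk of 30%, and assumed detection of 90% (active) and 50% (control).

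- Equal true risks: 45 × 0.3 × 0.9 = 12.2 active cases against 45 × 0.3 × 0.5 = 6.8 control cases.
- True ratio 0.7: 45 × 0.3 × 0.7 × 0.9 = 8.5 against 6.8.

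**Step 4: with the same enquiry in every arm.** If this makes detection equal, c = 1 and the reported ratio equals r.

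**The case against.** Several stronger readings are tempting, and the protocol does not support them.

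- *Events are captured weekly in the active arms and only at month 12 in controls.* A reader might infer this from the schedule, but no capture route is stated for any arm.
- *Treatment will look worse whatever the truth.* The arithmetic refutes this: with r = 0.7, c = 0.7 gives 1.00 and c = 0.9 gives 0.78. The direction of the bias is predictable; the sign of the reported difference is not.
- *The test-day script in Appendix D shows that nothing is asked at month 12.* That script includes signing consent and two measures (SPPB and PROMS) that Other Measures schedules before randomisation only. It reads as a baseline script, so its silence proves nothing about the 12-month visit.
- *A protective effect on falls would be reported as harm.* The sentence "The training group reduced the number of falls by 30% compared with the control group" is background literature on other populations. Falls are neither an outcome nor a named adverse event here, and no formal between-arm test of harms is stated.
- *The Monitoring section contradicts the adverse event section.* Sparse knowledge and an expectation of low risk can coexist. The two are in tension, not contradiction.

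A fair further point is that one value of c for all events is crude. Deaths and admissions may become known without sessions, and moves to a nursing home are asked about in all arms at 12 months. These would be less affected.

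What stands after all this is narrower: no common method of ascertainment is set, and contact is very unequal. That is a matter of data collection, so it belongs in the protocol.

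**Conclusion.** The concern holds in a limited form. The protocol promises complete noting and reporting of adverse events but fixes no way of finding them that is common to the three arms, while scheduled contact is about weekly in both active arms and undescribed for controls between baseline and month 12. Control events would probably be under-counted, and counts by arm biased against singing and exercise.

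The size is unknown. Ratios of 1.1, 1.4 or 2.0 under equal true risk correspond to assumed control detection at 90%, 70% or 50% of active detection and are illustrations, not estimates. The conclusion rests on one inference: that some events come to light through study contact. The consequence is confined to adverse event comparisons and low-risk statements by arm; the primary and secondary outcomes and the sample size are untouched.

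**What to change.** In Handling and Reporting of Adverse Events, add one short fixed question set (for example falls, injuries and hospital admissions), asked in the same words of participants in all three arms at the existing 12-month visit, and of a relative where available. Optionally repeat it at month 6, in the same mode in every arm, for instance by a brief telephone call.

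State that any between-arm comparison of harms rests on these answers only, and that events noted at sessions are listed separately without comparison. Align the risk wording under Monitoring with the statement that little is known about adverse effects.

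Cost: a few minutes at a visit that already takes place. The optional month-6 call would mean about 3 × 45 = 135 short calls at the recruitment target, and one light extra contact with controls, a small downside in a no-intervention arm. Some imbalance may remain, since regular sessions could still help active participants remember or report events; asking a relative should reduce it.

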## **Project Management and Time Line for the Project**

Project start: 1. March 2018

Data retrieval of pre-scanning, pretesting and similar before intervention: 01.02.2018 – 01.06.2018

Recruitment will be continuous until we reach our goal. Recruitment will start in March 2018.

Initiation of intervention will also be continuous and start as each participant is scanned and tested. Scanning and testing will be done from March until June, or longer if necessary.

Intervention period: 01.03.2018 – 01.03.2019

The intervention period may vary for the different participants, but not the length, which will last for 12 months. This means that if a participant joins the project on June 1, 2018, the intervention will begin from that date and last for 12 months from that date.

Analysis of brain imaging data: 01.02.2018 to 01.02.2020

Analysis of imaging data will occur on a continuous basis after each participant has been in the scanner and taken the psychological tests. Since this is to be done twice, it is assumed that much time will go for analysis. Statistical analysis comparing data between interventions will not commence before the end of data collection and preparation (database lock) for all participants.

Article writing and publishing of results: 01.02.2020 to 01.02. 2021

During this period, the project team will work on preparing data for publishing, creating guidelines/manuals for interventions that can be used by the municipality and the rest of the country. The intervention material, such as the music, the music program, the exercise program, will be made available for all who wish to use it, both domestic and internationally.

Recruitment end: 01.01.2020

Recruitment will be an ongoing procedure until we get 135 participants or the project run out of time. Hence the last day of recruitment will be a bit before a year is left of the project so that participants still get the 12 months of intervention and the analysis can be included.

Project end: 01.02.2021

Around the end of the project we wish to send out an evaluation form for participants where we ask if they are still home and whether they have moved into a nursing home. We will also ask if we can contact them two and a half years after intervention (which will be before the project ends) and then again 5 years after end of intervention.

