## **Secondary Behavioural Outcomes**

Title: Living independently at home

Description: A measure of when people with AD move to a nursing home

Time frame: 12 months (or longer)

Test: After 12 months of intervention we will ask our participants if they are still living at home or at a nursing home. We will also follow up with them after two and a half years and after five years to ask the same question. This is to get a deeper understanding of the longterm effects that music or exercise intervention may have on people with AD.

Title: Geriatric Depression Scale (GDS)

Description: Total score changes in the GDS which is a self-reported scale

Time frame: Testing before randomisation and after 12 months of intervention.

Test: GDS is a recognised test that is often used in psychological contexts and in research to gain and understanding of participants depressive symptoms or if they have depression. Depression is very common among the elderly. The GDS total score is the sum of 15 items, each of which is answered as yes (1) or no (0), the total score can range from 0 to 15. Higher scores indicates more severe depression symptoms. A score of > 11 indicates depression, with a sensitivity of 84 % and specificity of 95 %. However, for patients diagnosed with dementia (Burke, Houston, Boust, & Roccaforte, 1989), sensitivity and specificity has a somewhat lower cut-off score, which means that the test can only be used on people with light dementia, such as AD patients in early stages of the disease.

Title: Language abilities

Description: Word Learning Test

Time frame: Testing before randomisation and after 12 months of intervention.

Test: Language is one of the functions people with AD lose, and who often get worse with the disease. We want to see if our participants experience a recovery or not a deterioration through the intervention. Of course, this can also contribute to the effect of socialisation on a weekly basis, and that language is better taken care of by oral and interpersonal interactions. The reason we want to look at several parameters is to get an overview of what may be the different causes of change in the intervention.

Title: Sensor-motor functions

Description: Total score of the finger tapping test (FTT)

Time frame: Testing before randomisation and after 12 months of intervention.

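### The protocol's timeline contradicts itself: 12-month scans can fall up to 11 months after imaging analysis closes, the 2.5-year contact cannot precede project end, and the home-living outcome records no move date

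*Protocol*

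**What the plan says.** All the dates are in the protocol section Project Management and Time Line for the Project:

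- "Project start: 1. March 2018" and "Recruitment will start in March 2018".
- "Recruitment end: 01.01.2020". The reason given is that late recruits should still receive the full 12 months and be analysed.
- Intervention start may differ between participants, but the 12-month length may not.
- "Analysis of brain imaging data: 01.02.2018 to 01.02.2020".
- "Article writing and publishing of results: 01.02.2020 to 01.02. 2021".
- "Statistical analysis comparing data between interventions will not commence before the end of data collection and preparation (database lock"), a rule that covers all participants.
- Project end is 01.02.2021.
- Near project end, participants will be asked whether they may be contacted "two and a half years after intervention (which will be before the project ends"), and again five years after the end of intervention.

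Under Primary Outcomes, the second MR scan is at 12 months and depression change is measured over 12 months. Under Secondary Behavioural Outcomes, living independently at home is described as "A measure of when people with AD move to a nursing home". Its test is a question at 12 months, 2.5 years and 5 years about whether the person lives at home or in a nursing home.

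**The concern.** Three statements cannot all be followed if recruitment uses its permitted window: imaging analysis closes on 01.02.2020, writing of results opens that day, and nothing is compared between groups until everyone's data are locked. A team holding to the dates would be pressed either to look at group differences before lock or to compress processing, lock, analysis and publication into the last weeks.

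The 2.5-year contact belongs to a listed secondary outcome, and Specific Objectives names keeping people at home as long as possible as the project's goal. If the contact is scheduled and resourced on the belief that it falls within the project, nobody may be in place to make it. Even when it is made, the question asked gives status, not the time of moving that the outcome's description promises.

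**Working it through.** **Inputs.** All come from the time line unless stated: earliest intervention start 01.03.2018; recruitment end 01.01.2020; intervention length 12 months; second scan and GDS at 12 months (Outcomes); imaging analysis end and writing start 01.02.2020; project end 01.02.2021.

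**Step 1. The plan's own check.** The protocol says recruitment stops a little before one year is left. From 01.01.2020 to 01.02.2021 is 13 months, which is 12 months of intervention plus 1 month. That statement holds, so collection of the 12-month data fits inside the project.

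**Step 2. Last 12-month assessment against the analysis and writing dates.**
- Last scan and GDS = recruitment end + 12 months = 01.01.2020 + 12 months = 01.01.2021.
- Overrun of the imaging window = 01.02.2020 to 01.01.2021 = 335 days, or 11 months.
- Time left to project end = 01.01.2021 to 01.02.2021 = 31 days.
- Latest start with a 12-month scan by 01.02.2020 = 01.02.2020 − 12 months = 01.02.2019. Recruitment is allowed for another 11 months after that.

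**Step 3. The 2.5-year contact, counted from the end of intervention as the time line words it.**
- Earliest = 01.03.2018 + 12 + 30 months = 01.09.2021, which is 7 months after project end.
- Latest = 01.01.2020 + 12 + 30 months = 01.07.2023, which is 29 months after project end.
- Latest start that would satisfy the statement = 01.02.2021 − 42 months = 01.08.2017, before the project began.
- Taking 01.02.2018, the first day listed for baseline data, as the earliest start gives 01.08.2021, still 6 months late.

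**Step 4. The same contact counted from entry.** Latest start that satisfies the statement = 01.02.2021 − 30 months = 01.08.2018. Starts from then to 01.01.2020 still fail.

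**Step 5. How closely the home-living question can date a move.**
- Counted from entry, the contacts are at 12, 30 and 60 months. A move is placed only within an interval of 12, 18 or 30 months.
- Counted from the end of intervention, the later contacts are at 12 + 30 = 42 and 12 + 60 = 72 months. The intervals are 12, 30 and 30 months.

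**The case against.** The strongest reply is that these are administrative dates and the trial's data are safe. Much of that stands.

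- A reader might infer that the primary outcomes cannot be delivered. The protocol does not support this: Step 1 shows that every 12-month scan and GDS can be obtained before project end.
- A reader might infer that participants scanned after 01.02.2020 drop out of the analysis and that power falls with them. The protocol rules this out. The lock rule waits for all participants, and Statistical Methods analyses everyone randomised who has outcome data. The slip delays the analysis and does not shrink it.
- The 11 months and the 31 days are extremes. Baseline scanning is planned for March to June 2018, or longer if necessary. If all starts were by 01.06.2018, the last scans would fall on 01.06.2019, inside the window. Images are also processed as they arrive, and manuals and other preparation can begin before lock. But the protocol expressly permits recruitment to 01.01.2020, so its windows should work for that case.
- The five-year contact falls after project end on any reading, so contact beyond the project is already intended, and the mistaken parenthesis does not by itself prevent the 2.5-year contact. Secondary Behavioural Outcomes gives no explicit anchor, and counting from entry would bring the planned March to June 2018 intake inside the project. The time line's blanket statement is wrong even so.
- A reader might infer that home-living status is collected at unequal follow-up, because one form goes out around project end. That form is separate. The outcome itself is asked at fixed times per participant.
- The choice of time-to-event model may be left to the SAP. Whether a move date is collected at all is settled by the question the protocol sets.

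**Conclusion.** The concern holds as an internal inconsistency in the timeline, together with a mismatch between one outcome and its question. It does not show that data or power are lost.

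- **Analysis and writing windows:** up to 11 months too early, with as little as 31 days between the last assessment and project end. This assumes recruitment runs to its last permitted day; with faster recruitment the conflict shrinks or disappears.
- **2.5-year contact:** the statement that it precedes project end is wrong for every possible start as worded, by 7 to 29 months. This does not depend on recruitment speed. Counted from entry, it is true only for starts by 01.08.2018.
- **Home-living outcome:** described as when people move, but measured only as whether they have moved, at three widely spaced contacts.

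The protocol should be corrected on all three, because the corrections are cheap and let the trial measure the outcome it names.

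**What to change.** 1. Date database lock, imaging analysis and results writing from the last participant's 12-month visit, and reconcile them with recruitment end and project end. Either project end moves later or recruitment end moves earlier.
2. Delete the parenthesis stating that the 2.5-year contact precedes project end. State whether the 2.5- and 5-year contacts are counted from entry or from the end of intervention, and give the calendar range for each.
3. Obtain consent at enrolment for contact after project end, if the consent form does not already cover it, instead of waiting to ask near project end.
4. At each contact, record the date of any nursing-home move and the date of death, so that the outcome measures when people move. The analysis model can be set in the SAP.

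The cost is edits to the time line, one added question and possibly a later project end. An earlier recruitment end would instead mean restating the expected sample size and power.
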